**Fig. 1 Fig1:**
[figure not shown]
Timeline of intervention and outcome measurements

Participants receive 10 treatment sessions of daily AIH or daily SHAM. A single AIH session consists of 15, 90s episodes of breathing at a fraction of inspired oxygen (FiO_2_) of 0.10 ± 0.02 with 60s intervals of 0.21 ± 0.02 FiO_2_ (room air). While a single daily SHAM session consists of 15, 90s episodes of 0.21 ± 0.02 FiO_2_ with 60s intervals of 0.21 ± 0.02 FiO_2_ (room air). We provide the treatments via a custom air delivery system; see [10, 23, 32–34] for details. In brief, the delivery system directs a known air mixture from either a pressure-swing absorption (PSA) system [HYP-123; Hypoxico Inc., USA] or a blower source to the non-rebreather facemask. For safety, oxygen concentration within the breathing circuit is continuously monitored [OM-25RME; Maxtec Inc]. Additionally, we continuously monitor blood oxygen saturation (SpO_2_) and heart rate (HR) at 1-s intervals, and blood pressure (BP) every 5th breathing interval using a MASIMO system [MASIMO rainbow SET, Irvine, CA].
C.Walking practice

Walking practice sessions immediately follow (within 10 min) the breathing intervention and last for 60 min. Walking practice involves intensive training in walking-related functional tasks using a skill-based training approach. Recent studies found skill-based walking practice is more consistent with community walking, providing meaningful gains in walking function after neurologic injury [35–37]. Task-based walking practice replicates environmental challenges encountered during real-world walking [36] and corresponds to gains in walking balance, speed, and endurance that can be measured using the timed-up and go (TUG), 10-m walk test (10MWT), and 6-min walk test (6MWT), respectively [37]. The walking practice incorporates activities to develop skills in 5 walking-related task domains: 1) walking balance (e.g., walking on different surfaces), 2) skilled walking (e.g., negotiating obstacles), 3) walking with a secondary task (e.g., walking and carrying object), 4) endurance, and 5) speed [37].

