Pain severity: Using the five-point Wong-Baker FACES scale of 0 (no pain) to 5 (extreme pain) [44, 45].Spasticity: Using the Spinal Cord Assessment Tool for Spastic Reflexes (SCATS) [46], and the cumulative sum of three SCATS subscales: clonus (0 = no spasticity; 3 = severe), flexor (0 = no spasticity; 3 = severe), and extensor (0 = no spasticity; 3 = severe); and spasms using the Penn Spasm Frequency Scale (PSFS) [47].Blood pressure: At all pre-post treatment/assessment and follow-up time points. For each participant we specifically record hypertension incident rate, i.e. number of hypertensive events divided by units of person-measures (the sum of the total number of BP measurements), which accounts for the total number of chances for detecting a hypertensive event and for measurements not made due to dropout or a disqualifying adverse event [48]. We will also compute relative risk for participants within each group, i.e. hypertension incidence rate in the daily AIH subgroup over that in the daily SHAM and/or WALK groups [49], respectively, with a relative risk of one indicating no association between systemic hypertension incidence with interventions.Autonomic dysreflexia incident rate i.e. number of autonomic dysreflexia events divided by the total person-time (number of study days completed by each participant) to account for the total number of chances for detecting autonomic dysreflexia for days not measured due to dropout or a disqualifying adverse event [48]. We also compute relative risk within each group, as autonomic dysreflexia incidence rate in the daily AIH group over the incidence rate in the daily SHAM and WALK groups, respectively [49].

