Daily AIH ± WALK does not induce maladaptive changes (spasticity, pain, systemic hypertension, autonomic dysreflexia) in persons with subacute SCI. First, we predict no difference in SCATS following daily AIH ± WALK as compared to daily SHAM±WALK or WALK. We also predict no difference in the changes in FACES scores between interventions. We anticipate daily AIH alone or combined with walking practice will not elicit greater incidence of systemic hypertension in persons with subacute SCI. To test this hypothesis, we will compare the incidence rates of hypertension between interventions (daily AIH, daily AIH + WALK, daily SHAM+WALK, WALK) using Relative Risk [49, 52]. A Relative Risk of one will indicate no association between systemic hypertension and interventions. Using the 95% confidence interval of the Relative Risk [49], we will determine if there is a statistically significant association between interventions. We predict the relative risk of hypertension comparing daily AIH vs. daily SHAM, daily AIH + WALK vs. daily SHAM+WALK, and daily AIH + WALK vs. WALK are not different. We also predict the incidences of autonomic dysreflexia comparing daily AIH vs. daily SHAM, daily AIH + WALK vs. daily SHAM+WALK, and daily AIH + WALK vs. WALK are not different.

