### Adverse event reporting

The research team (PI, clinicians, and research assistants) reports adverse events related to each participant from the time of enrollment to the last follow-up assessment visit, which include: 1) unintentional loss of balance (i.e. fall to the ground), 2) change in systolic pressure to > 140 mmHg and/or diastolic pressure exceeding > 90 mmHg [55, 56], 3) autonomic dysreflexia with systolic blood pressure > 150 mmHg or > 20 mmHg from baseline with complaints of headache, diaphoresis, and/or blurred vision, 4) musculoskeletal injury during/after walking training (i.e. sprain, fracture, etc.), 5) symptoms such as pain, soreness, numbness, or signs of injury (inflammation, blisters, etc.) during or immediately following training or on returning home, 6) hospitalization for any cause, and 7) death due to any cause.

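### Hypothesis 3 tests repeatedly measured blood pressure only as a rate of hypertensive events; a baseline-adjusted analysis of the pressures should be added beside it

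*Protocol article*

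**What the plan says.** The protocol article collects blood pressure often. Under Outcome measures: "Blood pressure: At all pre-post treatment/assessment and follow-up time points". Under Intervention (Breathing treatment), sessions also include "blood pressure (BP) every 5th breathing interval using a MASIMO system". Outcome measures says that both the magnitude and the frequency of pain, spasticity, hypertension and autonomic dysreflexia are measured.

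The summary for hypertension is a rate: "number of hypertensive events divided by units of person-measures (the sum of the total number of BP measurements". The only level that could define an event is in the list under Adverse event reporting: "change in systolic pressure to > 140 mmHg and/or diastolic pressure exceeding > 90 mmHg".

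Statistical analysis, Hypothesis 3, aims at this conclusion: "Daily AIH ± WALK does not induce maladaptive changes (spasticity, pain, systemic hypertension, autonomic dysreflexia) in persons with subacute SCI". For hypertension the test is: "we will compare the incidence rates of hypertension between interventions (daily AIH, daily AIH + WALK, daily SHAM+WALK, WALK) using Relative Risk". The decision rule is: "Using the 95% confidence interval of the Relative Risk [49], we will determine if there is a statistically significant association between interventions". The only reference value is the null: "A Relative Risk of one will indicate no association between systemic hypertension and interventions". No margin is given, and the predicted result is no difference. No model for the pressure values is stated. For the walking outcomes, Hypothesis 2 does specify a mixed model with subject as random effect, differences from baseline, and ANCOVA if baselines differ.

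**The concern.** Counting readings above a cut discards how far each reading moved and where the participant started. A rise that stays under the cut contributes nothing. A participant whose usual pressure lies near the cut contributes events whatever the treatment does. The article says that magnitude is measured but attaches no between-arm analysis to it.

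At stake is the safety statement of Aim 3. With small arms and no margin, a non-significant relative risk could be read as showing that AIH does not raise pressure, when the analysis had little chance of showing a moderate sustained rise. The readings needed for a more informative answer are already being collected.

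**Working it through.** The article states no power, event rate, pressure SD or margin for Aim 3, so there is no figure of its own to reproduce.

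**Arm size** (Sample size section, 12% attrition, equal allocation assumed)
- Aim 1: 34 × 0.88 = 29.9, about 30 in two arms, 15 per arm.
- Aim 2: 51 × 0.88 = 44.9, about 45 in three arms, 15 per arm.

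**Assumptions, none of them in the article**
- Mean SBP 115–125 mmHg.
- Between-person SD τ = 10–15, within-person SD σ = 10, person-specific drift SD δ = 5–8.
- 28 on-study and 2 baseline readings per participant.
- Event = SBP > 140, two-sided 5% level.

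**Sustained rise, by simulation.** AIH adds the same amount to every on-study reading.

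| True rise | Event rates (participant-level rank test) | Mean SBP adjusted for baseline |
|---|---|---|
| 10 mmHg | 0.27–0.58 | 0.71–0.92 |
| 5 mmHg | 0.10–0.20 | 0.24–0.39 |

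Type I error was near 0.05 for both.

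**Closed-form check of the last column**
- Variance of a participant's on-study mean: V = τ² + δ² + σ²/28.
- Residual variance after adjustment: R = V − τ⁴/(τ² + σ²/2).
- Standard error of the arm difference: √(R × 2/15).
- τ = 10, δ = 5: V = 128.6, R = 128.6 − 66.7 = 61.9, SE = 2.87. For 10 mmHg, 10/2.87 = 3.48 and power is 0.92. For 5 mmHg, 1.74 and 0.39.
- τ = 15, δ = 8: V = 292.6, R = 292.6 − 184.1 = 108.5, SE = 3.80. For 10 mmHg, 2.63 and 0.72. For 5 mmHg, 1.31 and 0.25.

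These agree with the simulated ends of the range.

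**Where the gain comes from** (10 mmHg). The unadjusted column uses √(V × 2/15); the other two are simulated.

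| Setting | Event rates | Mean SBP, unadjusted | Mean SBP, baseline-adjusted |
|---|---|---|---|
| Mean 115, τ = 10, δ = 8 | 0.42 | SE 4.73, power 0.53 | 0.73 |
| Mean 125, τ = 15, δ = 5 | 0.33 | SE 5.81, power 0.38 | 0.87 |

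Dropping the cut adds 0.05–0.11; using the participant's own baseline adds 0.20–0.49. A second set of assumptions shows the same order (24 readings, no drift, mean 110–130, between-person SD 8–15, within-person SD 8–12). For 10 mmHg it gives 0.34–0.77 for event counts, 0.42–0.90 for unadjusted means and 0.92–0.999 for adjusted means.

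**Brief spikes instead of a sustained rise** (first set of assumptions). If AIH adds 30 mmHg to 10% of readings, the mean moves by only 0.10 × 30 = 3 mmHg. Power is then 0.17–0.63 for event rates and 0.11–0.18 for adjusted mean SBP. With 40 mmHg spikes it is 0.25–0.87 and 0.16–0.27.

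**How the relative-risk interval is computed.** The denominator is a count of readings. If the interval treats those as independent, the false-positive rate at zero effect is roughly 0.34–0.62 over both sets of assumptions. An interval clustered by participant brings it to 0.06–0.12 under the second set.

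**The case against.** A reader might infer that a real pressor effect will probably be missed and AIH then declared free of hypertension, and that the event rate should give way to mean pressure. The documents do not support that, for these reasons, which all stand.

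- **Effect shape.** The power advantage assumes a uniform shift, the most favourable case for a mean. Aim 3 is about hypertension and autonomic dysreflexia, and Safety precautions is concerned with rapid changes in pressure. For episodes the event rate is the better detector. The article supports neither shape over the other.
- **Direction of error.** The article does not say how the interval is computed. A participant-level interval makes misses the main risk; an interval that treats readings as independent makes false alarms the main risk.
- **The question asked.** The hypothesis for hypertension concerns incidence, and a rate comparison answers it. A mean difference answers a different, complementary question.
- **Other causes.** Small arms and the missing margin remain. Even the adjusted analysis misses a 5 mmHg rise in 61–76% of trials (1 − 0.39 to 1 − 0.24).
- **Unseen text.** The article is condensed. A summary of pressure values may exist elsewhere, and the eligibility table, which would show how many participants start near the cut, is not visible. The participant's own baseline is also not ignored throughout Aim 3: the autonomic dysreflexia definition includes a rise from baseline.

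These points limit the claim but do not remove it. The article does fix a between-arm test for blood pressure. That test uses neither size nor baseline, while the article says that magnitude is measured.

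**Conclusion.** The gap is real and moderate in weight. The one between-arm blood pressure test that the article fixes has low power for a sustained rise when analysed by participant: about 0.27–0.58 for 10 mmHg and 0.10–0.20 for 5 mmHg with 15 per arm. Baseline-adjusted mean SBP reaches 0.71–0.92 and 0.24–0.39. The figures depend on the assumed pressures and SDs, equal allocation and a constant shift. Most of the gain is due to baseline adjustment rather than to dropping the cut alone, and it reverses for brief spikes. The finding is therefore that the event rate should not stand alone. It is not that the event rate is wrong, nor that a harmful effect will be missed.

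**What to change.** In Hypothesis 3:

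1. Keep the hypertensive-event rate and relative risk as the test of incidence, and state that the 95% interval is clustered by participant. With 15 per arm, a small-sample correction or a participant-level permutation test is advisable, given the 0.06–0.12 found above.
2. Add a mixed model of SBP and one of DBP. Restrict both to time points scheduled identically in the compared arms, because the WALK arm has no breathing sessions. Use arm, visit and arm-by-visit as fixed effects, baseline pressure as covariate and subject as random effect.
3. Report the difference in mmHg with its 95% interval for AIH vs SHAM, AIH+WALK vs SHAM+WALK, and AIH+WALK vs WALK.
4. Base the blood pressure safety statement on both analyses and on which rises the interval excludes, not on non-significance alone. Under the assumptions above the half-width for mean SBP would be about 2.05 × 2.87 = 5.9 to 2.05 × 3.80 = 7.8 mmHg, so an observed difference of zero would exclude rises above roughly 6–8 mmHg.

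Cost: one extra analysis on data already recorded and no new measurement. A mean difference is clinically less direct than an event rate and insensitive to brief episodes, which is why both are reported.

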### Hypothesis and aims

The fundamental hypothesis guiding this study is that repetitive exposure to AIH (10 sessions in 2 weeks) will enhance walking recovery in ambulatory and non-ambulatory persons with subacute SCI, presumably by augmenting neural plasticity through a combination of spontaneous neural recovery and AIH-mediated spinal mechanisms. To test this hypothesis, we are carrying out three specific aims: 1) to quantify the impact of daily AIH (alone) on restoring walking ability in persons with subacute SCI who are initially unable to walk overground, 2) to quantify the beneficial effects of daily AIH with walking practice (daily AIH + WALK) on improving walking ability in persons with subacute SCI who are initially able to walk overground and 3) to determine if the benefits of daily AIH in persons with subacute SCI are without evidence of maladaptive changes and pathology (e.g. hypertension, autonomic dysreflexia, pain, and spasticity) [10, 23].

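### Hypothesis 3 claims no harm but its only stated test looks for a significant relative risk, with no margin and no stated allowance for repeated readings within a person

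*Protocol article*

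**What the plan says.** In the protocol article, Aim 3 (Hypothesis and aims) is "to determine if the benefits of daily AIH in persons with subacute SCI are without evidence of maladaptive changes and pathology". Under Statistical analysis, Hypothesis 3 reads: "Daily AIH ± WALK does not induce maladaptive changes (spasticity, pain, systemic hypertension, autonomic dysreflexia) in persons with subacute SCI".

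For hypertension the article says the hypothesis will be tested by comparing incidence rates through a relative risk. It adds: "A Relative Risk of one will indicate no association between systemic hypertension and interventions". The decision step is "Using the 95% confidence interval of the Relative Risk [49], we will determine if there is a statistically significant association between interventions". The expected result for the ambulatory arms is that the relative risks for "daily AIH + WALK vs. daily SHAM+WALK, and daily AIH + WALK vs. WALK are not different", with the same prediction for AIH against SHAM alone. For autonomic dysreflexia, spasticity (SCATS) and pain (FACES) the text only predicts no difference.

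Outcome measures defines the hypertension rate as "number of hypertensive events divided by units of person-measures (the sum of the total number of BP measurements"), taken before and after treatments and assessments and at follow-ups. Dysreflexia uses study days as its denominator. The same section says "For each participant we specifically record hypertension incident rate", but not how participants are combined. A subject random effect is named for Hypothesis 2 and nothing comparable for Hypothesis 3. Sample size concerns walking outcomes only.

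**The concern.** There are two separate problems.

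**The test does not match the claim.** A test against a relative risk of 1 can show harm but cannot show its absence. Without a limit on what is tolerable, an interval that includes 1 may also include a doubling or more. If Hypothesis 3 is taken as supported whenever no significant association appears, a small trial makes support easy to obtain.

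**The unit of the rate is not the randomised unit.** People who tend to be hypertensive contribute several hypertensive readings each. An interval that counts every reading as independent overstates the information and can produce a difference from chance imbalance between a few individuals.

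The two act in opposite directions: the first gives false reassurance, the second false alarm. Which one occurs depends on how readings are combined, which the article does not say. What Aim 3 can conclude is at stake.

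**Working it through.** The article gives no event rate, margin or power for safety, so there is no planned figure to reproduce. Rates and correlations below are assumptions, shown over a range.

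**Inputs**
- Participants per arm: Aim 1 has 34 × 0.88 = 29.9 in two arms and Aim 2 has 51 × 0.88 = 44.9 in three (Sample size; equal allocation assumed). Both give n = 15.
- Readings per person: before and after 10 treatment days gives 20. The listed visits (1 + 10 + 3 = 14) give 28. Range used: m = 20 to 30.
- Assumed: control rate p0 of 15% or 10% of readings; ICC of 0.05, 0.1 or 0.3.

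**Step 1: an interval that ignores clustering, true relative risk 1.** The design effect is DE = 1 + (m − 1) × ICC. The standard error is too small by √DE, so the chance that the interval excludes 1 is 2 × [1 − Φ(1.96/√DE)].

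| ICC | DE, m = 20 | excludes 1 | DE, m = 30 | excludes 1 |
|---|---|---|---|---|
| 0.05 | 1.95 | 16% | 2.45 | 21% |
| 0.1 | 2.9 | 25% | 3.9 | 32% |
| 0.3 | 6.7 | 45% | 9.7 | 53% |

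Beta-binomial simulation (20,000 trials per cell, p0 = 15%) agrees to within about a point: 16–21%, 24–31% and 45–53%.

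**Step 2: width of a valid interval.** For an observed ratio of 1, SE = √[DE × 2(1 − p0)/(p0 × n × m)]. With p0 = 0.15 and m = 30, the naive SE is √(1.7/67.5) = 0.159, and the 95% interval is 0.73–1.36. Multiplying the SE by √3.9 (ICC 0.1) gives 0.54–1.85. Multiplying by √9.7 (ICC 0.3) gives 0.38–2.63, which does not rule out a doubling.

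**Step 3: a valid interval when the rate truly doubles.** SE = √{DE × [(1 − 2p0)/(2p0) + (1 − p0)/p0]/(n × m)}, and the chance that the interval still includes 1 is 1 − Φ(ln 2/SE − 1.96). Example with p0 = 0.15, m = 20, ICC 0.1: SE = √(2.9 × 8.0/300) = 0.278; 0.693/0.278 − 1.96 = 0.53; missed in 30%.

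| ICC | p0 15%, m = 20 | p0 15%, m = 30 | p0 10%, m = 20 | p0 10%, m = 30 |
|---|---|---|---|---|
| 0.05 | 14% | 9% | 34% | 26% |
| 0.1 | 30% | 25% | 50% | 46% |
| 0.3 | 63% | 61% | 75% | 74% |

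Simulation with standard errors taken from the spread between participants and a t reference on 28 degrees of freedom stays within about three points. At p0 = 15% a doubling is missed in about 9–32% of trials (ICC 0.05–0.1) and about 65% (ICC 0.3). At 10% the figures are about 28–52% and 75%. The false-positive rate of this interval is about 5–6% at p0 = 15%, rising to 7–8% at 10% with ICC 0.3.

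**The case against.** Several stronger readings are tempting, and the article does not support them.

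- **That the plan declares AIH safe whenever the interval includes 1.** No such sentence is written. The text predicts and anticipates, and Aim 3 asks only about absence of evidence. What stands is that the hypothesis is one of no harm, the article says it will be tested this way, and it states no other route to confirmation.
- **That the intervals are wrong.** The formula sits in a cited source that is not shown, the rate is recorded per participant, and a separate analysis plan may deal with clustering. The article therefore supports only a conditional statement: the intervals are too narrow if a standard formula is applied to pooled readings.
- **That the trial would nearly always miss a doubling.** That follows from classing each person as hypertensive or not. With 3 of 15 in each arm, for example, the interval is 0.24–4.18. The article specifies events over readings instead. If those are pooled naively, a true doubling is flagged in most trials: in simulation with 30 readings each, about 87–99% at a 15% control rate and 77–93% at 10%. The failure there is false alarm.
- **That in-session readings distort the comparison with WALK.** Breathing treatment does describe monitoring of "blood pressure (BP) every 5th breathing interval", but as safety monitoring. Outcome measures sets the outcome at pre/post and follow-up times, so these readings are not shown to enter the rate.

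It is also fair to say that this is a phase II trial sized for efficacy. A safety monitoring board, a medical monitor and itemised adverse-event reporting protect participants during conduct, but they do not change what the Hypothesis 3 comparison can show.

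**Conclusion.** The point holds in a limited form. The mismatch between a no-harm hypothesis and a difference test without a margin is in the text and needs no assumption beyond the approximate arm size. The clustering point is conditional on pooled readings being analysed with a standard interval; the false-positive rate would then be roughly three to ten times the nominal 5% over the range examined. Using a valid interval exposes the first problem fully: depending on the assumed rate and ICC, a true doubling would go undetected in anything from about a tenth to three-quarters of trials. Under neither analysis would a non-significant relative risk establish absence of harm. The explicit interval rule covers hypertension only, but the no-difference predictions for dysreflexia, SCATS and FACES invite the same misreading.

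**What to change.** Before the comparative data are examined:

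1. State that the hypertension and dysreflexia rate ratios will be estimated with the participant as the unit of clustering. Options are negative binomial regression, GEE Poisson with a log offset for number of readings or study days, or a bootstrap by participant. With about 15 per arm, add a small-sample correction to robust standard errors.
2. Use the pre/post and follow-up readings already defined under Outcome measures.
3. Report each estimate with its upper confidence limit, and say that non-significance will not be read as absence of harm. Then choose one of two routes. Either present safety as estimation only, or conclude no maladaptive change only if the upper limit lies below a margin set in advance by the sponsor and the safety board, and otherwise report the result as inconclusive. A formal margin is optional; the wording is not.
4. Apply the same wording to dysreflexia, SCATS and FACES.

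This needs no new data and no change to procedures. The price is wider intervals and a more modest safety statement.
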